### Active malaria case detection and asymptomatic infection survey

Clinical malaria will be identified through active case detection. A cohort of 150 households, which includes about 500 residents based on our previous surveys in the same area (household size of 3.35 or 14,824/4420 persons/household), will be selected randomly from each cluster, and all residents in the selected households will be recruited upon signing consent/assent forms for participation. Written informed consent/assent (for minors under age of 18) for study participation will be obtained from all consenting heads of households and each individual who is willing to participate in the study. Inclusion criteria are provision of informed consent/assent and no reported chronic or acute illness except malaria. Exclusion criteria are individuals who are unwilling to participate or infants under the age of 6 months. Participants will be visited every 2 weeks and screened for clinical malaria. A clinical malaria case is defined as an individual with fever (axillary temperature of 37.5 °C or higher) and other related symptoms such as chills, severe malaise, headache, or vomiting at the time of examination or 1–2 days prior to the examination, in the presence of a *Plasmodium*-positive blood smear.

During each visit, a project field team consisting of a lead laboratory technician, a community health volunteer, and a field assistant will talk to the matriarch, who has information on the health status of every resident in the household, to check if any resident in the household has experienced fever within the last 48 h or is suspected to have malaria. For all fever and suspected malaria cases, blood will be taken and thin and thick smears prepared on a labeled slide. Body temperature will be taken with a digital thermometer, and the symptoms and signs of the illness will be recorded on a case report form (CRF). Clinical cases will be referred to the nearest government-run hospital or health center for free treatment. Each participant will be assigned a unique identification number corresponding to their household and cluster. Each participant will also receive an identity card, which can be used to obtain free malaria treatment at the hospital or health center whenever they have a fever or believe they have malaria.

Asymptomatic malaria infection is important for malaria control. To determine the impacts of interventions on malaria infection prevalence, we will collect finger-prick blood samples as described in baseline surveys. Study subjects are selected from the same households as the active case detections. Finger-prick blood samples will be collected on blood slides and on filter papers for PCR analysis, i.e., to determine infection status. The survey will be done twice a year, once in the rainy season and another time during dry season. Age and sex of participants will be recorded.

We masked field staff, who will conduct the active case detections and collect blood samples and mosquito samples in the cross-sectional surveys, to the study groups the clusters were assigned to. However, it is not possible to mask either the investigators or the participants to the treatment allocation of indoor residual spraying.

### Informed consent, ethical clearance, and conflict of interest statement

Ethical clearance has been obtained from the Ethical Review Committee of Maseno University, Kenya (MSU/DRPI/MUERC/00778/19), and the Institutional Review Board (IRB) of the University of California, Irvine, USA (HS# 2017-3512). Written consent will be obtained from all participants. Written assent for children (< 18 years of age) will be obtained from the participants and their parents or guardians. Inclusion criteria are as follows: provision of informed consent (assent for children) and no reported chronic or acute illness other than malaria. Exclusion criteria are as follows: unwillingness to participate in the study or reported chronic or acute illness other than malaria. Permission to use microbial larvicides for malaria vector control has been obtained from the Pest Control Products Board of Kenya. All investigative team members in the USA and Kenya have no financial conflict of interest with the larvicide manufacturer, Central Life Sciences.

### Malaria vector population monitoring

We will conduct malaria vector population surveillance on a seasonal basis continuously until at least 12 months after the stage 2 intervention (Fig. 2). We will monitor both indoor- and outdoor-biting mosquito abundance using non-baited CDC light traps. We will set up two traps within each sampling compound: one inside the living room and the other outside the house 5 m away. We will conduct a total of 40 trap-nights (20 indoor and 20 outdoor) of vector sampling per cluster per season. Species of collected mosquitoes will be identified, and blood-feeding status will be recorded. We will test for *P. falciparum* sporozoite infection and blood meal source using an enzyme-linked immunosorbent assay (ELISA) on all specimens [55]. For each house where the vector population is sampled, we will record the number of sleeping persons at the house on the day of the vector survey. We will calculate the sporozoite rate and EIR for each cluster. The EIR will be calculated as (number of *Anopheles* per person) × (average number of persons bitten by one *Anopheles* in 1 day) × (sporozoite rate) and standardized to a seasonal basis. We will calculate indoor and outdoor transmission intensities separately, assuming that all mosquitoes collected from a compound had their blood meal from the same household. We will calculate the EIR for each cluster, if possible, or for each block. In addition to population monitoring, we will also conduct insecticide resistance monitoring twice a year.

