#### Primary and secondary endpoints

The primary endpoint is clinical malaria incidence rate. The secondary endpoints are malaria vector abundance and transmission intensity. A clinical malaria case is defined as an individual with fever (axillary temperature of 37.5 °C or higher) and other related symptoms such as chills, severe malaise, headache, or vomiting, in the presence of a *Plasmodium*-positive blood smear. Clinical malaria incidence rate is calculated as the number of clinical malaria episodes divided by the total person-time (person-years) at risk based on demographic surveys. Malaria vector abundance is measured as the total density of malaria vector mosquitoes (*An. gambiae* s.s., *An. arabiensis*, *An. funestus*, and other new species capable of transmitting malaria) collected indoors by CDC miniature light traps. Malaria transmission intensity is measured as the sum of the indoor entomological inoculation rates (EIRs).

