#### Cross-sectional vector abundance and malaria infection prevalence

To determine malaria infection prevalence, cross-sectional finger-prick blood samples will be collected on blood films and on filter papers for PCR analysis, following the nested PCR method for dried blood spots based on the 18S rRNA gene to detect the malaria species [54, 57, 58]. In western Kenya, the major rainy season is usually from April to July and the major dry season is from November to March next year. To minimize the seasonality effect, we will conduct vector abundance and parasite prevalence surveys twice a year, once in June/July and another time from November to January.

All clusters will be examined for mosquito abundance. We have previously determined that the CDC light trap is an efficient sampling tool [55, 59]. For each cluster, we will conduct adult mosquito collections in 10 houses for 10 nights per month. *An. gambiae* s.l. and *An. funestus* s.l. will be analyzed by rDNA-PCR for species identity [60, 61]. All specimens will be tested for *Plasmodium* sporozoite infection using PCR [62, 63], and blood meal analysis will be performed by PCR [64–66]. Aquatic habitats within the 0.5-km buffer zone of the study cluster will be mapped using GPS and examined for *Anopheles* larval and pupal abundance using standard dippers [67]. A subset of larvae will be reared to adults and used to test resistance to pyrethroid and organophosphate insecticides using the standard WHO insecticide susceptibility bioassay [68]. *Plasmodium falciparum* isolates from the community-based and hospital-based surveillance will be genotyped at *Pfmdr*1 for lumefantrine tolerance and at *PfKelch*13 for artemisinin resistance [69].

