### Data analysis

Differences in clinical malaria incidence and vector abundance between the treatment and control groups will be analyzed using Poisson multivariate regression models with intervention, malaria risk, cluster, and calendar time as covariates, using a generalized estimating equation (GEE) approach with population at each cluster as an offset [96]. GEE is necessary because incidence will be modeled monthly as a longitudinal measure using grouped data. Intervention will be a time-varying covariate, since the treatment in a cluster may be adapted and readapted depending on the response to the previous treatment. The odds ratio and 95% confidence interval for clinical malaria rates between the treatment groups and the control group will be calculated. For the second aim analysis (estimation of outcomes for the 4 embedded adaptive interventions), weighted and replicated generalized estimating equations will be used to estimate the mean clinical malaria incidence rates among the 4 embedded adaptive interventions and to compare the slopes at each stage for each adaptive intervention. Here, weighting is necessary to account for the potential over- or underrepresentation of some groups (e.g., non-responders would have a 1/4 chance of following their assigned treatment sequence, whereas responders would have a 1/2 chance of following their assigned treatment sequence) [97, 98].

We will identify a final intervention strategy after all cost and effectiveness data are collected. The aim of this strategy will be to recommend an optimal intervention method given the local conditions at each site. For this purpose, we will adopt the *Q*-learning framework from the previous section on enhanced machine learning methods [99]. We will train a neural network to predict each method’s utility, accounting for both effectiveness (reduction in malaria incidence rate) and cost based on the conditions at each site, such as malaria risk and socioeconomic, entomological, and genetic features. All data collected throughout this research will be used to train the final model. To reduce model complexity, we will consider clustering sites into a small number of classes and then training a model to predict the efficacy of each method conditioned on each class. Once the *Q*-function is learned, we will identify the optimal intervention by choosing the intervention method that maximizes the learned *Q*-function.

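### The block-level fallback for EIR removes the treatment contrast, and the vector-abundance model uses human population where trap-nights are the exposure

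*Protocol article*

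**What the plan says.** All references are to the protocol article.

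- **Endpoint definitions** (Primary and secondary endpoints). Vector abundance is a density of vectors caught indoors in CDC light traps. For the other secondary endpoint, "Malaria transmission intensity is measured as the sum of the indoor entomological inoculation rates (EIRs").
- **Unit of EIR** (Malaria vector population monitoring). The section first says, without condition, "We will calculate the sporozoite rate and EIR for each cluster". It later says "We will calculate the EIR for each cluster, if possible, or for each block". No criterion is given for when the cluster level is not possible.
- **Blocks** (Cluster stratification for interventions; Initial cluster randomization). There are three blocks, of low, intermediate and high transmission. Each ideally has 12 clusters, four per intervention.
- **Model** (Data analysis). "Differences in clinical malaria incidence and vector abundance between the treatment and control groups will be analyzed using Poisson multivariate regression models". Intervention, malaria risk, cluster and calendar time are covariates, and the population of each cluster is the offset for both outcomes.
- **Trapping effort.** The baseline section (Cross-sectional vector abundance and malaria infection prevalence) says "we will conduct adult mosquito collections in 10 houses for 10 nights per month". The monitoring section says "We will conduct a total of 40 trap-nights (20 indoor and 20 outdoor) of vector sampling per cluster per season".
- **Sporozoite assay.** The baseline section specifies "sporozoite infection using PCR [62, 63], and blood meal analysis will be performed by PCR". The monitoring section specifies "sporozoite infection and blood meal source using an enzyme-linked immunosorbent assay (ELISA) on all specimens".
- **Use of baseline data** (Baseline surveys for cluster randomization). They serve stratification and will also be used to evaluate the interventions.

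**The concern.** Two stated rules do not fit the endpoints they serve.

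First, randomisation was within block, so every block contains every arm. An EIR computed per block mixes the treatments that the endpoint is meant to compare. The trial's hypothesis names transmission risk as well as incidence, so losing the arm contrast on EIR would leave half of it without its main entomological measure. The fallback would most plausibly be invoked when infected mosquitoes are few, although the article does not say so.

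Second, an offset in a Poisson model declares what the count is a rate of. Human population is right for clinical cases. For mosquitoes in traps the exposure is trap-nights, and dividing by residents gives a quantity different from the density defined as the endpoint.

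The differences in effort and assay matter only if baseline and follow-up entomology are combined, but the article leaves that open.

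**Working it through.** The article gives no power or event figure for the entomological endpoints, so there is none to reproduce.

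**1. Block fallback.** Inputs: 12 clusters per block, 3 arms, 20 indoor trap-nights per cluster per season.

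- Clusters per arm within a block: 12 / 3 = 4.
- Indoor trap-nights per block per season: 12 × 20 = 240, of which 4 × 20 = 80 come from each arm.
- EIR at cluster level: 36 values, 12 per arm. EIR at block level: 3 values, none attributable to an arm.

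**2. How sparse might a cluster be?** Assumption, not in the article: 2 vectors per trap-night, so 20 × 2 = 40 specimens per cluster-season. The chance of no positive specimen is (1 − s)^40 for sporozoite rate s.

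| s | 40 specimens (one cluster) |
|---|---|
| 1% | 0.99^40 = 67% |
| 2% | 0.98^40 = 45% |
| 5% | 0.95^40 = 13% |

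Pooling the four clusters of one arm within a block gives 160 specimens; at s = 1% the chance is 0.99^160 = 20%. So sparse cluster data are plausible, and pooling within arm relieves them while keeping the contrast.

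**3. Offset, single clusters.** Cluster size is about 500 to 1000 inhabitants (Study area and cluster selection). An equal catch of 40 gives 40/500 = 0.08 and 40/1000 = 0.04 per resident, a ratio of 2.0 at identical trap density. This compares two clusters, not two arms.

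**4. Offset, arm comparison.** Simulation of 12 v 12 clusters, 4,000 replicates per scenario. Assumed: population uniform on 500 to 1000, 20 trap-nights per cluster, 2 vectors per trap-night, log-normal variation in density between clusters. Each arm's rate is Σcount / Σoffset. The log rate ratio is tested with a robust variance on 22 degrees of freedom. With equal effort, a trap-night offset is a constant and equals no offset.

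| Between-cluster SD of log density | SE under no effect: trap-nights / population | Power at true ratio 0.5: trap-nights / population |
|---|---|---|
| 0.3 | 0.138 / 0.157 | 99.4% / 97.8% |
| 0.5 | 0.226 / 0.240 | 83.9% / 79.6% |
| 0.8 | 0.376 / 0.385 | 50.0% / 47.8% |

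The mean estimated ratio is 0.50 with either offset. Type I error is about 5% to 7% with either.

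Hand check at SD 0.5. The squared coefficient of variation of counts is (e^0.25 − 1) + 1/(40e^0.125) = 0.284 + 0.022 = 0.306. That of population is (500²/12)/750² = 0.037. The SE is √(2 × 0.306/12) = 0.226 without the population offset and √(2 × 0.343/12) = 0.239 with it, in agreement with the simulation.

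**5. Cluster as fixed effect.** In a simulated panel with cluster and time effects, the log ratio was −0.686 with and without the population offset. A population constant over time is fully absorbed.

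**6. Effort.** If the baseline sentence means one trap per house per night, effort is 10 × 10 = 100 collections a month against 20 indoor trap-nights a season. That is at least five-fold in raw counts, even if a season were only one month.

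**The case against.** The strongest reply is that cluster-level EIR is the stated default and the block level only a conditional fallback. That stands: as planned by default, each arm has 12 EIR values. The trigger for the fallback is not stated, and its link to effective control is an inference.

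On the offset, the two-fold figure concerns pairs of clusters, and randomisation spreads population across arms. If cluster enters as a fixed effect, as the covariate list allows, a constant population drops out. If population means the surveillance cohort, it is about 150 × 3.35 ≈ 500 in every cluster and the offset is nearly constant. All of this stands, and it limits the harm to noise and a mislabelled scale.

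On effort and assay, neither differs by arm, and no endpoint is defined as a change in EIR from baseline. Concurrent comparisons between arms are therefore not biased.

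A reader might infer two stronger things. One is that the entomological endpoints in general cannot show an arm effect. The article does not support this: it is true only of EIR, and only under the fallback. The other is that the outdoor catches go unused. They do not: the monitoring section calculates indoor and outdoor transmission intensity separately. Indoor-only secondary endpoints are a design choice, and that they favour nets and spraying over larval source management is untested.

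What the reply does not answer is that a block EIR cannot compare arms, and that residents are not the exposure for a trap count.

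**Conclusion.** The point holds in a limited form. The block-level fallback, if used, leaves a named secondary endpoint with three values per season and no treatment contrast. This follows from the randomisation scheme alone and needs no outside assumption. How often the fallback would be needed is unknown; the illustration rests on an assumed catch and assumed sporozoite rates.

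The population offset is mis-specified for vector counts. Its cost is about 2 to 4 points of power under the assumed catch, variation and population spread, with no systematic bias between arms, and nothing if cluster is a fixed effect and population is constant over time.

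The effort and assay statements need reconciling and are not in themselves a bias between arms. Response status, sample size and cost-effectiveness ratios rest on clinical incidence, so none of this touches the primary analysis. It should be corrected before the entomological analysis.

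**What to change.** 1. **EIR.** Keep it at cluster level. A cluster with tested specimens and no positive has an estimated EIR of zero, which can stay in the analysis. If pooling is needed, pool within block only among clusters with the same assigned regimen, never across arms. In stage 1 that is the randomised arm. In stage 2 it is the embedded adaptive intervention or the stage 2 subgroup, because pooling by stage 1 arm would mix responders with re-randomised non-responders. Under the article's assumed 1:1 response ratio, four clusters split on average into two responders and one in each second-stage option, so within-block pooling by subgroup gains little there. State the trigger for pooling in advance.
2. **Vector abundance.** Specify a separate count model with log(trap-nights) as offset, and keep population for clinical incidence.
3. **Reconciliation.** State which trapping effort and which sporozoite assay apply to each period. Before baseline EIR or abundance enters any evaluation, put both periods on the same effort scale and the same assay.

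Naming outdoor abundance or EIR as a secondary endpoint is optional; the data are already to be collected.

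Items 1 and 2 cost a few sentences and a change in analysis code, with no new fieldwork. Item 3 costs laboratory work only if the two periods really do use different assays.

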### Cluster stratification for interventions

For each cluster, we will determine vector abundance and malaria infection prevalence. Malaria risk in each cluster will be predicted based on the predictive features (variables) described above. We plan to adopt two approaches for risk prediction. The first approach (classification-based) will first stratify the study clusters into distinct strata based on weighted vector abundance and malaria infection prevalence using *k*-means or hierarchical clustering algorithms [75]. A classifier will be trained to predict risk-group assignments based on predictive variables. To avoid overfitting, we will first try classification models with low complexities, such as naïve Bayes, softmax, and support vector machines (SVM) to establish a baseline, and then move to more complex models, such as decision trees, random forests, and neural networks [76–81]. The second approach (regression-based) will directly predict prevalence and malaria transmission intensity based on the predictive variables using Gradient Boosting (GB) linear and logistic regression (LogitBoost) or an ensemble of regression trees [82]. Each method has pros and cons. The classification-based approach is easier to interpret and less prone to overfitting, but the cluster assignment may not be clear-cut. On the other hand, although it does not require cluster assignment, the regression-based approach must model prevalence and vector abundance separately and is thus more prone to overfitting with nonlinear models [83].

The data from all study clusters (36 initially) will be split into a training set and a validation set, with model parameters trained on the training set and performance evaluated on the validation set. Tenfold cross-validation will be performed to maximally utilize the data [84, 85]. For the classification task, we will determine each model’s sensitivity and specificity and use the auROC (area under ROC curve) to measure model performance. For the regression task, we will use the mean-square loss to measure model performance. Trained models will be further tested and refined on data from 36 different clusters collected in year 2 and future years.

The goal is to stratify all clusters into 3 blocks during the initial intervention stage: low transmission, intermediate transmission, and high transmission.

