### Trial design and outcome measures

#### Initial cluster randomization

The SMART trial design includes two intervention stages (Fig. 2 and Table 1). Based on pre-intervention malaria risk analysis, study clusters will be stratified into three blocks with different risk levels as described above. In each block, clusters will be randomly assigned with equal probability to one of the three interventions in stage 1, i.e., LLIN, PBO LLIN, and LLIN + IRS (Fig. 2). Cluster randomization will be done using computer-generated random numbers. Ideally, each block will include 12 clusters and each of the three interventions will be assigned to four clusters in each block (Fig. 1).

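### The fallback of calculating the EIR per block pools all intervention arms, so wherever it is used it cannot inform the comparison of interventions on transmission intensity

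*Protocol article*

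**What the plan says.** The protocol article, under Primary and secondary endpoints, states: "The secondary endpoints are malaria vector abundance and transmission intensity". It measures transmission intensity by summing the indoor EIRs. The Hypothesis section expects the adaptive approach to lower transmission risk as well as incidence.

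The rule for calculating the EIR is under Malaria vector population monitoring. That section first says without condition that the sporozoite rate and EIR will be obtained for every cluster. It then adds a proviso: "We will calculate the EIR for each cluster, if possible, or for each block". It does not say what would make a cluster value impossible.

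Two other sections fix what a block is. Cluster stratification for interventions says: "The goal is to stratify all clusters into 3 blocks during the initial intervention stage", and names them low, intermediate and high transmission. Initial cluster randomization repeats that "study clusters will be stratified into three blocks with different risk levels as described above" and continues: "In each block, clusters will be randomly assigned with equal probability to one of the three interventions in stage 1". Ideally, "each block will include 12 clusters and each of the three interventions will be assigned to four clusters in each block".

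**The concern.** The block is the unit within which the interventions are randomised, so it is the one pooling unit certain to mix them. An EIR per block describes a risk stratum, not an intervention. If cluster values are replaced by block values in some seasons or strata, those data cannot contribute to any comparison between LLIN, PBO LLIN and LLIN + IRS, or between the stage 2 options.

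At stake is one of two named secondary endpoints and the transmission half of the hypothesis. The Data analysis section names comparison models for clinical incidence and vector abundance only. The monitoring section is therefore the only place in the article that fixes how the EIR is formed, and nothing elsewhere restores the arm contrast.

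**Working it through.** The article gives no figure for EIR precision or power, so there is no stated number to reproduce. The check is structural, with simple arithmetic.

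**1. Composition of a block in stage 1.** Inputs are 36 clusters, 3 blocks and 3 arms (Initial cluster randomization). 36 / 3 = 12 clusters per block, and 12 / 3 = 4 clusters per arm per block.

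**2. What a block EIR can show.** With equal weight per cluster, block EIR = (4 × LLIN + 4 × PBO LLIN + 4 × LLIN+IRS) / 12. Take an illustrative control EIR of 10:

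| True situation | Calculation | Block EIR |
|---|---|---|
| No effect in either arm | (40 + 40 + 40) / 12 | 10.00 |
| Only PBO LLIN halves the EIR | (40 + 20 + 40) / 12 | 8.33 |
| Only LLIN + IRS halves the EIR | (40 + 40 + 20) / 12 | 8.33 |
| Both halve it | (40 + 20 + 20) / 12 | 6.67 |

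The second and third rows cannot be told apart. Other weights would change the values, but there would still be one number per block and none per arm. The fallback gives three values, one for each risk stratum.

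**3. Stage 2.** The Sample size justification assumes a 1:1 response ratio. Of 12 clusters starting on PBO LLIN, 6 would be non-responders, 3 per second-stage option, or about 1 per block. The same holds for LLIN + IRS. Assuming the LLIN clusters stay as they are, a block of 12 would hold about 4 LLIN, 2 PBO LLIN responders, 1 + 1 re-randomised from PBO LLIN, 2 LLIN + IRS responders and 1 + 1 re-randomised from LLIN + IRS. That is seven groups in one average.

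**4. What pooling by group would keep.** Trapping effort is 20 indoor trap-nights per cluster per season (Malaria vector population monitoring).
- Stage 1, arm within block: 3 × 3 = 9 values, each from 4 clusters and 4 × 20 = 80 indoor trap-nights per season.
- Stage 1, arm across blocks: 3 values, each from 12 clusters and 12 × 20 = 240 indoor trap-nights.
- Stage 2, re-randomised option across blocks: about 3 clusters and 3 × 20 = 60 indoor trap-nights. Within a block this is about one cluster, so pooling within block gains almost nothing there.

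**5. How often the fallback would be used.** This cannot be derived. The section's formula is a product of mosquitoes per person, persons bitten per mosquito per day, and sporozoite rate. A cluster with mosquitoes but no positives therefore has an EIR of 0, which is calculable. The sporozoite rate is undefined only when no mosquito is caught.

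The documents give neither catch density nor sporozoite rate, so I assume 0.5 to 5 vectors per indoor trap-night and 0.5% to 3% positive:
- Expected catch per cluster-season: 20 × 0.5 = 10 to 20 × 5 = 100 mosquitoes.
- P(no mosquito) at the lowest density, Poisson: exp(−10), about 0.00005. Overdispersed catches would raise this.
- P(no positive) = exp(−20 × density × rate): exp(−0.05) = 95% at the low end and exp(−3.0) = 5% at the high end.

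The last line shows that zero-positive cluster-seasons could be common. It does not show how often the authors would treat the cluster EIR as impossible.

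**The case against.** The strongest defence is that the cluster is the stated unit, without condition, one sentence earlier, and the block is only a contingency. The endpoint sums EIRs, so one sparse season would not remove it. No passage plans an arm comparison on block values, and the analysis of the EIR may sit in a fuller document. The authors may also have meant arm within block.

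Much of this stands. Where cluster values are obtained, the comparison is intact, and the contingency may prove rare. It does not rescue the rule itself. The article does not leave the pooling unit open: it states one, and its own definition of a block makes that unit mix the arms. No passage supports reading it as arm within block.

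A reader might infer three stronger points, which the documents do not support:
- **That the fallback would be used often.** The 5% to 95% range is the chance of no positives under assumed inputs. Under the section's own formula, such clusters have an EIR of zero, not a missing one.
- **That the proviso depends on the outcome, so effective interventions lose their cluster values and benefit is hidden.** The article gives no trigger, and it aggregates clusters rather than dropping them.
- **That each arm would be credited with the block average.** Nothing plans to assign block values back to arms.

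**Conclusion.** The point holds in a limited form. Wherever the block fallback is applied, the EIR contains no between-arm information and cannot contribute to comparing interventions on transmission intensity. In stage 2 it also merges responder and re-randomised groups. This follows from the article's definition of a block and needs no numerical assumption; only the stage 2 group sizes rest on the 1:1 response ratio.

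The overall impact is unknown, because neither the trigger nor the mosquito yield is given. Clinical malaria incidence, its power calculation and vector abundance do not depend on this rule. It is a rule for one secondary endpoint that should be corrected, and it does not threaten the trial's main result.

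**What to change.** In Malaria vector population monitoring, replace the block fallback with pooling by intervention group within block, or by intervention group across blocks where cells are too small, as they will be in stage 2. State that the EIR is never pooled across arms. State also that a cluster with mosquitoes but no sporozoite-positive specimen has EIR = 0 and is not treated as not calculable, and give the criterion for any pooling that remains.

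Any model for the EIR should keep the per-person definition in that section, for which the number of sleepers per house is already recorded. A count of positives per trap-night would be a different endpoint.

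The change is a sentence or two and needs no new data. The price is precision: a within-block value in stage 1 rests on about 4 rather than 12 clusters. If cluster values were equally variable, its standard error would be √(12/4) ≈ 1.7 times that of the block mean, and stage 2 values would be less precise still. The more precise block mean, however, does not answer the question about interventions.
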